### Procedure

For the participants who meet the inclusion criteria, the researchers will introduce the research content to them to confirm their willingness to participate in the study. Participants will also be asked whether they understand the benefits and possible risks involved in this study. For participants who agree to join in the study, the researchers will ask them to download the App and researchers will issue an informed consent form and inform participants that they will be randomly assigned to different groups, and all the individuals have the right to consult to researchers. If the participant does not agree to be involved in the study, the researchers will record the reasons for their refusal. The schedule of enrolment, interventions, and assessments are summarized in Table 2. If the intervention was shown to be effective, participants in the control group would receive the intervention immediately after the study was completed.

**Table 2 Tab2:** The timeline of enrolment, interventions and assessments

	Study period										
	Enrolment	Allocation	Intervention						Follow-up		
Timepoint		t_0_	1st week	2nd week	3rd week	4th week	5th week	6th week	t_1_	t_2_	t_3_
Enrolment:											
eligibility screen	●										
informed consent	●										
allocation		●									
Interventions:											
intervention group			●	●	●	●	●	●			
control group			●	●	●	●	●	●			
Assessments:*											
baseline		●									
immediately after the last intervention									●		
3 months following the intervention										●	
6 months following the intervention											●

*Variables assessed at baseline include demographic factors, socioeconomic factors, depression status, negative emotion symptoms, parenting competence

*Variables assessed at other three times are the same, they were depression status, negative emotion symptoms, parenting competence

### Randomization

The allocation scheme is generated by the random digital program. The whole randomization process is a computer-based algorithm. The starting value will be determined by the current server time and the process of the allocation scheme will be recorded for replication. Randomization will not be stratified and will occur automatically at the completion of the baseline survey by obtaining the next allocation of the generated timeline.

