## Methods/design

### Design

A double blind, randomized controlled trial (RCT) will be used in this study. All participants who met the inclusion criteria were randomly assigned to the intervention group or control group for a six-week intervention program.

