### Participants

This study will be conducted in Changsha city, which has five administrative district. We will randomly select one health center from all the community health centers in each district. Participants will be recruited from five community health centers we selected. Inclusion criteria:has Established maternal health care record in community health centers;0 days to 6 weeks after delivery;Score of 9–12 on the Edinburgh Postnatal Depression Scale (EPDS);Access to smart phone and able to independently use App;Informed consent and voluntary participation.

Exclusion criteria:Severe mental disorders (current or in the past);History of brain injury, intellectual disability or cognitive disorder; andUndergoing psychotherapy or any other psychological intervention.Patients diagnosed with postpartum depression or other severe mental illness during the study.

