### Sample size

A power analysis was performed for linear regression using University Dusseldorf G*Power 3.1 to determine the sample size necessary for analysis. The main objective of this study is to assess the effectiveness of App-based CBT on PPD high-risk mothers. According to previous studies, an effect size of 0.43 will be adopted [40]. The power analysis based on the conventional significant alpha level of 0.05 and a power of 0.90 using a two-tailed test. We calculate that the sample size required is 48 in each group. Considering a 20% dropout rate, the recruited sample size required in each group is 60.

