### Analysis

This study used double data entry. Data entrants, analysts, and data custodians do not participate in the intervention process. Analyses will be performed using SPSS (version 20.0; SPSS Inc., Chicago, Ill). All tests of significance will be determined at an alpha level of 0.05. The principle of ITT will be used to handle missing data. We plan to analyse contrasts between intervention and control groups at baseline, post intervention, 3 months and 6-months follow-up.

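### Randomisation is fixed as unstratified although women come from five separately selected health centres: valid, but it gives up a small and nearly free gain in precision

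*Protocol article*

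**What the plan says.** Under Participants, the protocol article describes how the sample is built: "We will randomly select one health center from all the community health centers in each district". Changsha has five districts, so "Participants will be recruited from five community health centers we selected". Centre is therefore part of the sampling design and is known for every woman before she is allocated.

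The unit of allocation is the individual (Design): "All participants who met the inclusion criteria were randomly assigned to the intervention group or control group". The Randomization section describes a fully computer-based process that runs once the baseline survey is finished, and adds the rule at issue: "Randomization will not be stratified and will occur automatically at the completion of the baseline survey". No reason is given for not stratifying.

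On the comparison itself, the Analysis section says: "We plan to analyse contrasts between intervention and control groups at baseline, post intervention, 3 months and 6-months follow-up". It names no model and no covariates, and it neither includes nor excludes centre. The Sample size section gives the analytical setting for the power calculation: "A power analysis was performed for linear regression using University Dusseldorf G*Power 3.1".

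**The concern.** In a trial of 120 women spread over five centres, each centre contributes few women. Without stratification, the intervention share can differ a good deal from one centre to another, even if the overall split ends at exactly 60:60. If centres also differ in mean EPDS, DASS-21 or C-PSOC score, that imbalance moves the treatment estimate by chance, and the between-centre differences stay in the error term unless centre is fitted.

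What is at stake is precision and tidiness of interpretation. A visible imbalance within a centre also invites an unplanned decision about adjusting for centre once data are in. Since a program already does the allocation, avoiding both would take very little.

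**Working it through.** **Inputs from the document.** 48 per group required, 20% dropout, 60 per group, 120 in total; five centres; individual 1:1 allocation; no strata. The dropout step reproduces: 48 / (1 − 0.20) = 60, and 2 × 60 = 120. The document gives no figure for centre imbalance, so there is none to reproduce.

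**Assumptions, none in the document.** Equal centres, 120 / 5 = 24 women each. Simple allocation, each woman having probability 0.5 of either arm. Intraclass correlation (ICC, the share of outcome variance due to centre) of 0, 0.02, 0.05 or 0.10. Total outcome SD set to 1.

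**Step 1: how often centres are unbalanced.** For one centre the number in the intervention arm is Binomial(24, 0.5).

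- 16:8 or worse: 2 × 1,271,626 / 2^24 = 0.152. In at least one of five: 1 − (1 − 0.152)^5 = 0.56.
- 15:9 or worse: 2 × 2,579,130 / 2^24 = 0.307. In at least one of five: 1 − (1 − 0.307)^5 = 0.84.

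**Step 2: how far centre alone can move the estimate.** With five centres the overall mean cancels between arms, so only 4/5 of the centre variance matters. The SD of the shift is √(4 × ICC × 0.8 / 120).

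- ICC 0.05: √(0.16 / 120) = 0.0365; × 1.96 = ±0.072 SD.
- ICC 0.10: √(0.32 / 120) = 0.0516; × 1.96 = ±0.101 SD.

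**Step 3: total sampling error.** Unstratified and unadjusted, the variance is 4 × (1 − ICC/5) / 120, times about 1 + 1/120 = 1.008 because the overall split is itself random. Stratified with a centre term, it is 4 × (1 − ICC) / 120. The ratio is (1 − ICC) / (1 − ICC/5) / 1.008.

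| Assumed ICC | Variance ratio | Reduction | 95% half-width, unstratified | 95% half-width, stratified + centre |
|---|---|---|---|---|
| 0 | 1 / 1 / 1.008 = 0.99 | 1% | | |
| 0.02 | 0.98 / 0.996 / 1.008 = 0.98 | 2% | | |
| 0.05 | 0.95 / 0.99 / 1.008 = 0.95 | 5% | 0.358 | 0.349 |
| 0.10 | 0.90 / 0.98 / 1.008 = 0.91 | 9% | 0.356 | 0.339 |

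Simulation with 5 × 24 women and 60,000 trials per scenario gave ratios of 0.98, 0.97, 0.955 and 0.92 for the same ICCs, which agrees closely.

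**Step 4: adjusting without stratifying.** In the same simulation, adding a centre term to an unstratified trial gave ratios of 1.035, 1.02, 0.99 and 0.95. At low ICC the term costs a little, because the arms are unbalanced within centres. Stratifying removes that cost.

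**Step 5: validity of the present rule.** In 8,000 simulated trials per scenario (overall split fixed at half and half, ICC 0 to 0.10, 96 or 120 women, equal or unequal centres), the analysis without centre had type I error 0.047 to 0.054. Its mean estimate was 0.428 to 0.436 for a true 0.43.

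**Step 6: sensitivity to unequal centres.** If centres contributed 60, 24, 16, 12 and 8 women (assumed), the sum of squared shares is 0.25 + 0.04 + 0.0178 + 0.01 + 0.0044 = 0.322, which replaces 1/5 in the formula. The ratio is 0.95 / 0.984 / 1.008 = 0.96 at ICC 0.05 and 0.90 / 0.968 / 1.008 = 0.92 at ICC 0.10. The conclusion does not change.

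**The case against.** The case for leaving the rule alone is substantial. Unstratified individual randomisation is a legitimate design. Chance imbalance between centres is part of the sampling error that the ordinary standard error already covers, and step 5 shows no bias and no inflation of type I error. All of this stands.

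The gain is also small. At ICC 0.05 the 95% half-width falls from 0.358 to 0.349. One could describe a shift of 0.072 or 0.101 SD as 17% or 24% of the 0.43 in the Sample size section (0.072 / 0.43 and 0.101 / 0.43). That singles out one component of random error, and the article does not state that 0.43 is a standardised mean difference. The fair comparison is with the total of ±0.36.

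Nor does the document point to a large centre effect. All centres are in one city, entry is restricted to EPDS 9–12, both arms receive their modules through the App, and outcomes after baseline are collected in it. The centres recruit rather than deliver, so the lower ICCs may be nearer the truth.

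A reader might also infer that the plan compares the arms without centre. The text does not support this. The Analysis section lists no covariates and excludes none, linear regression can carry a centre term, and an article commonly leaves covariates to the full protocol or analysis plan.

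What the objection does not remove is that the allocation rule is stated outright, without a reason, and that stratifying with a centre term showed no loss of precision at any ICC examined.

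**Conclusion.** The point holds as a minor design improvement. The Randomization section declines a stratification that the five-centre sampling invites and that the existing program could supply. The cost is a variance about 1–2% higher than it need be at ICC 0–0.02, about 5% at ICC 0.05 and 8–9% at ICC 0.10. These figures rest on assumed ICCs, about 24 women per centre and simple allocation. If the overall split were held at 60:60, the factor 1.008 would drop out, and the gain would be nil at ICC 0 and about 4% and 8% at ICC 0.05 and 0.10 (0.95 / 0.99 = 0.96; 0.90 / 0.98 = 0.92).

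The stronger conclusion that unstratified allocation biases or invalidates the comparison is not supported.

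**What to change.** In the Randomization section, replace the unstratified rule with a computer-generated list in permuted blocks of varying size, stratified by the five health centres. In the Analysis section, state that the between-group comparisons include centre as a fixed factor, so that the standard error reflects the stratification.

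The cost is one setting in the allocation program and four degrees of freedom: 118 becomes 114 with 120 women, or 94 becomes 90 with 96. Blocking makes the next assignment slightly more predictable. Varying block sizes and automatic release after the baseline survey limit this.

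If recruitment has already begun unstratified, the allocation need not be disturbed. The centre term can still be specified before outcomes are seen, on the understanding that without stratification it costs about 3.5% in variance at ICC 0 and saves about 5% at ICC 0.10.

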### Blinding

This study will be a double-blind trial. After the baseline survey is completed, the allocation scheme will be generated by a computer program and it will be kept in closed and opaque envelopes and saved by the researchers who have no direct relationship with the project to ensure that the random allocation scheme is hidden in advance. The automatic randomization allocation of the participants will remain blind to the enrolling researcher. Researchers who administered the six-week intervention and analyzed the data were also blind to the grouping. Participants will be informed that this study is to investigate the effectiveness of an App-based intervention program to protected women from PPD, but they will not be informed of anything content related to the specific interventions.

### Analysis

This study used double data entry. Data entrants, analysts, and data custodians do not participate in the intervention process. Analyses will be performed using SPSS (version 20.0; SPSS Inc., Chicago, Ill). All tests of significance will be determined at an alpha level of 0.05. The principle of ITT will be used to handle missing data. We plan to analyse contrasts between intervention and control groups at baseline, post intervention, 3 months and 6-months follow-up.

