**Methods:**

A double blind, randomized controlled trial will be used in this study to examine the effectiveness of App-based CBT in reducing the prevalence of postpartum depression compared with usual postpartum care in China. A total of 120 participants will be recruited in this study. The intervention consists of a weekly theme module app for continuous six weeks, each module including learning content and assignments. The control group received usual postpartum care content through the App. Outcome measures include postpartum depression, anxiety, pressure and parenting sense of competence at 0-, 3- and 6-month after the intervention.

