### Measures

Measurements will be obtained at baseline (t_o_), immediately after the last intervention (t_1_), 3 months following the intervention (t_2_) and 6 months following the intervention (t_3_). The baseline data is collected when participants are enrolled, and after that, the data collection process will be implanted in the evaluation module of the mobile App. The primary outcome will be depression status. The secondary outcomes will be negative emotion symptoms including depression, anxiety and stress, parenting confidence. These will be measured as follows:*Demographic and Socioeconomic factors:* the information about Risk factors will be collected by demographic questioner including pregnancy and birth history, obstetric complications, delivery mode, baby gender, baby weight, baby health status, feeding pattern, satisfaction with family care, major life events. The socioeconomic factors include maternal age, marital status, history of depression, family history of mental disorder, occupation, medical insurance, education level, family income, and religious belief.*Depression status:* We will use the Edinburgh Postnatal Depression Scale (EPDS) Chinese version to assess participant’s depressive status, as this scale is an effective self-screening tool for PPD. The EPDS to be used in this study was translated by Lee [35] the sensitivity was 82%, the specificity was 86%, the positive predictive value was 44%, and the negative predictive value was 97%. The scale includes 10 items. The recommended threshold is < 9: no depression; 9 is regarded as a probable case; and 13 or more as suspected depression.*Negative emotion symptoms:* We will assess negative emotion symptoms using the Depression, Anxiety and Stress Scale (DASS-21), which is a self-report measure of anxiety, depression and stress levels used in diverse settings developed by Lovibond [36]. The Chinese version of DASS-21 was developed by Taouk ^[40]^ in 2001. This version was tested in Australian-Chinese speaking samples and Hong Kong-Chinese speaking samples, and indicated that the items had been adequately and appropriately translated and adapted. Wen Yi et al. [37] tested DASS-21 in 730 Chinese adults (over 18 years old), the result showed that the Cronbach’s α was 0.912 and the test-retest Pearson correlation coefficient was 0.751.*Parenting competence:* Parenting competence will be assessed using the Chinese version of Parenting Sense of Competence Scale (C-PSOC). The initial Parenting Sense of Competence Scale was an English version developed by Gibaud-Wallston [38]. In 2014 Chinese researcher, Yang Xiao translated it into Chinese and applied to Chinese population. C-PSOC includes efficacy and satisfaction factors and has 17 items. The Cronbach’s coefficient, efficacy factor and satisfaction factor of C-PSOC were 0.82, 0.80 and 0.85 respectively [39].

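### ITT is named as the method for missing data, which it cannot handle; with 20% dropout planned and follow-up described only through the App, the contrasts could rest on completers or carried-forward scores

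*Protocol article*

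**What the plan says.** The Analysis section of the protocol article gives one sentence on missing outcomes: "The principle of ITT will be used to handle missing data". It then plans comparisons between the groups at baseline and at each of the three follow-up visits. It names no mixed model, imputation, carry-forward or completer rule.

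The Sample size section allows for loss: "Considering a 20% dropout rate, the recruited sample size required in each group is 60". That figure is built on 48 analysable women per group ("We calculate that the sample size required is 48 in each group").

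The Measures section says that, after baseline, "the data collection process will be implanted in the evaluation module of the mobile App". The description of the intervention condition also places all four surveys inside the App. No other route for follow-up data is described.

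The Participants section admits women with an EPDS score of 9 to 12. It also lists, among the exclusions, women who receive a diagnosis of postpartum depression or other severe mental illness while the study is running. The Measures section makes EPDS depression status the primary outcome and gives thresholds of 9 and 13.

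**The concern.** The sentence assigns a task to a principle that cannot perform it. ITT says that every randomised woman is counted in the arm to which she was allocated. It does not say what stands in for an EPDS score that is missing at the end of the intervention, at 3 months or at 6 months. An analyst who follows the sentence literally still has to choose something. Separate contrasts at each visit invite either using whoever answered or filling the gap with an earlier score and calling the result ITT.

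Three features of the design make that choice matter.

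- **Planned loss.** One woman in five is expected to drop out, and the sample size is built on those who remain.
- **Collection route.** Follow-up answers come through the same App that delivers the modules. A woman who leaves the App may also stop supplying outcomes. The two arms receive different content, so this could differ by arm.
- **Narrow entry range.** Baseline EPDS lies just between the two thresholds, so a carried-forward baseline score fixes the woman's classification in advance.

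The exclusion of women diagnosed during the study is a further difficulty. If it is applied after randomisation, it removes women for a reason tied to the primary outcome, and that conflicts with an ITT analysis.

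**Working it through.** **1. The plan's own figure.** Inputs from the Sample size section: 48 per group after loss, 20% dropout. 48 / (1 − 0.20) = 60 per group, or 120 in total. This reproduces the stated number. Planned loss is 0.20 × 120 = 24 women, 12 per group. The stated power therefore refers to women with outcome data and not to all who are randomised.

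**2. Classification under carry-forward of baseline.** Entry EPDS is 9, 10, 11 or 12. Each of these is at or above 9, and none reaches 13. For any woman with no EPDS after baseline, carry-forward makes her a case at 9 and a non-case at 13, whatever happened to her. A woman with at least one follow-up score would, under last observation carried forward, keep that later score, which can take any value.

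**3. Dilution with equal loss.** The article adopts an effect size of 0.43 without stating its metric. Assume here that it is a standardised mean difference. Baseline means are equal by randomisation, so women with carried-forward baseline contribute no difference. With a fraction m carried forward in each arm and the SD held constant, the effect is (1 − m) × 0.43 = 0.80 × 0.43 = 0.344.

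**4. Power.** Two-sided alpha 0.05, noncentral t, df = 2n − 2, noncentrality d × √(n/2).

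| Analysis | n per group | d | Noncentrality | Power |
|---|---|---|---|---|
| Completers as planned | 48 | 0.43 | 2.11 | 55% |
| Baseline carried forward for 20% | 60 | 0.344 | 1.88 | 46% |
| No loss at all | 60 | 0.43 | 2.36 | 65% |

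The like-for-like comparison is 46% against 55%, because the plan expects 48 per group with data.

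**5. How far the constant SD matters.** Carried-forward scores are confined to 9 to 12 and so have little spread. Assume a carried-forward mean of 10.5 and SD of 1.1, a follow-up SD s of 3 to 5, and a control follow-up mean of 8 to 11. The variance in an arm with observed mean μ is 0.8 s² + 0.2 × 1.1² + 0.16 × (μ − 10.5)². Averaging this over the arms and dividing 0.8 × 0.43 × s by its square root gives 0.34 to 0.38 SD, and power at 60 per group of 46% to 54%. The 46% is therefore the lower end.

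**6. Unequal loss, illustration only.** Assumptions: SD 4, true difference 0.43 × 4 = 1.72 points, carried-forward mean 10.5, control follow-up mean 8.5 or 10.5.

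- Loss of 30% in the App arm and 10% in control, control mean 8.5: control 0.9 × 8.5 + 0.1 × 10.5 = 8.70; App 0.7 × 6.78 + 0.3 × 10.5 = 7.896; difference 0.804, or 0.20 SD. With control mean 10.5: 10.5 − (0.7 × 8.78 + 0.3 × 10.5) = 1.204, or 0.30 SD.
- The reverse imbalance gives 1.948 points (0.49 SD) and 1.548 points (0.39 SD).
- Completers only, if women lost score 2 to 4 points worse than those retained: bias = difference in loss × shift. Equal loss gives 0. With 30% against 10%, 0.2 × 2 = 0.4 and 0.2 × 4 = 0.8 points, or 0.1 to 0.2 SD. This favours the arm with the greater loss.

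**The case against.** The strongest reply is that the choice of missing-data method is commonly left to a full protocol or analysis plan, neither of which is shown, so its absence from an article is no fault. That is right about absence. It does not rescue the sentence, which gives a rule and gives the wrong one. A plan that names a method elsewhere would still leave this sentence to be corrected.

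Several stronger readings are tempting, and the article does not support them.

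- **That the primary result will rest on completers or on a carried-forward score.** Neither method is named, and a mixed model or multiple imputation is not ruled out. Only that it could is supported.
- **That all 24 lost women would be cases at 9 and none at 13.** This needs all 24 to lack any EPDS after baseline. The 20% is not tied to a visit, and there are three follow-ups.
- **That women are lost because of the intervention or their mood.** No reasons for dropout are given. Both arms complete six App modules, and the surveys form a separate section of the App, so skipping modules need not mean skipping surveys. That the App is the sole route is itself an inference from no other being described.
- **That power falls from 65% to 46%.** The 65% assumes 60 per group with no loss, which the plan does not expect.

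Equal loss in the two arms does not by itself imply bias. It is also fair to say that a mixed model on EPDS scores presumes a continuous outcome, while the article calls the primary outcome depression status.

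**Conclusion.** The point holds as a misstated rule whose consequences are possible but not established. ITT cannot handle missing data, and the sentence needs correcting whether or not a method is named elsewhere. The planned loss of 24 women is large enough for the choice of method to change the result.

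If baseline were carried forward for 20% of each arm, 0.43 SD would become about 0.34 SD (up to 0.38 SD once the narrow spread of carried-forward scores is allowed for). Power would be about 46% (up to 54%), against 55% with 48 completers per group. These figures rest on reading 0.43 as a standardised mean difference. Under unequal or outcome-related loss the estimate could move in either direction by the amounts illustrated, which depend on assumed SDs, means and loss rates. The article neither shows nor excludes such loss. The fixed classification at 9 and 13 applies only to women with no EPDS after baseline.

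**What to change.** - **Define ITT.** State that it means all randomised women, analysed in the arm to which they were allocated. Reconcile this with the listed exclusion of women diagnosed during the study.
- **Name the missing-data method separately.** For EPDS as a score, use a likelihood-based mixed model over the three follow-up visits with baseline EPDS, visit, and visit by arm; SPSS, the stated software, offers this as MIXED. If the primary outcome is binary depression status, use multiple imputation. Either should replace any single-value carry-forward.
- **Add a delta-shift sensitivity analysis.** Make unobserved EPDS scores worse by a stated range, in the App arm alone and in both arms. The article gives no basis for the range, so it should be declared as an assumption.
- **Protect follow-up.** Keep sending the follow-up questionnaires to women who stop the modules, for example by a link that does not depend on module use. Record stopping the App separately from withdrawing from follow-up.

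The cost is a little more analysis work, a few sentences of text and a questionnaire link.

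### The plan lists a between-group contrast at baseline among its significance tests and gives the pre-randomisation outcome scores no stated role as covariates

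*Protocol article*

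**What the plan says.** The planned comparison is one sentence in the Analysis section of the protocol article: "We plan to analyse contrasts between intervention and control groups at baseline, post intervention, 3 months and 6-months follow-up". The same section adds: "All tests of significance will be determined at an alpha level of 0.05". It names no test, model or covariate.

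The notes to Table 2 (Procedure section) list what is available at t0: "Variables assessed at baseline include demographic factors, socioeconomic factors, depression status, negative emotion symptoms, parenting competence". The three outcome domains are assessed again at t1, t2 and t3. The Randomization section fixes the order of events: "Randomization will not be stratified and will occur automatically at the completion of the baseline survey".

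Two other sections bear on the point. Participants restricts entry to EPDS scores of 9 to 12. Sample size says: "A power analysis was performed for linear regression using University Dusseldorf G*Power 3.1", without naming predictors.

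**The concern.** There are two linked problems.

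**The baseline contrast.** It stands in the same list as the efficacy contrasts, under a test level that covers all tests, so the natural reading is that baseline differences will be tested. Allocation comes after the baseline survey. If randomisation works as described, the null hypothesis of that test is true by design, and its p-value says nothing about the App. The practical risk is that a chance p-value below 0.05 prompts covariates to be chosen after the fact, or that a p-value above 0.05 is taken to show that no adjustment is needed.

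**The unused baseline scores.** Every outcome has a pre-randomisation measurement, but the only role stated for it is as one more time point to contrast. As a covariate it would reduce the residual variance of the follow-up comparison and account for chance imbalance in that score. At stake is the precision of the follow-up estimates, not their validity.

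**Working it through.** The plan gives no figure for either problem, so there is none to reproduce. The sample-size figure enters only in step 4.

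**1. Chance findings at baseline.** The baseline scores are EPDS, the three DASS-21 scales (depression, anxiety, stress) and C-PSOC, which makes five. With a true null and level 0.05 for each:

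- P(at least one significant) = 1 − 0.95^5 = 1 − 0.774 = 0.226, about 23%.
- If the two C-PSOC factors are tested separately there are six scores: 1 − 0.95^6 = 0.265.
- If EPDS enters as a category using the article's thresholds (below 9, from 9, and 13 or more), every eligible woman is in the same category at t0. No baseline comparison of it is then possible, and four scores remain: 1 − 0.95^4 = 0.185.

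Independence is assumed. Positive correlation among the scores would generally lower these probabilities.

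**2. Gain from the baseline covariate, DASS-21 and C-PSOC.** Adjusting for a baseline value with correlation ρ to the follow-up value multiplies the variance by 1 − ρ². The article does not give ρ, so a range is assumed:

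- ρ = 0.3: 1 − 0.09 = 0.91, a 9% reduction
- ρ = 0.5: 1 − 0.25 = 0.75, a 25% reduction
- ρ = 0.7: 1 − 0.49 = 0.51, a 49% reduction

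**3. Gain from the baseline covariate, EPDS.** Entry allows only four scores, 9 to 12.

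- If they are evenly spread, the baseline SD = √((4² − 1)/12) = √1.25 = 1.118.
- Within the trial, ρ = slope × 1.118 / follow-up SD.
- Assumed slope 0.5 and SD 5: 0.5 × 1.118 / 5 = 0.11, and ρ² = 0.01.
- Assumed slope 1.0 and SD 4: 1.0 × 1.118 / 4 = 0.28, and ρ² = 0.08.

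Baseline EPDS alone therefore removes about 1 to 8% of the variance. A range-restriction calculation gives a similar answer: an unrestricted correlation of 0.5 to 0.7 and an unrestricted SD of 4 to 5 (both assumed) leave ρ at about 0.13 to 0.26, a reduction of about 2 to 7%.

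**4. Would adjustment rescue the sample size?** Read the stated effect size of 0.43 as a standardised mean difference. The article does not say which metric it is. For two-sided 0.05 and 90% power:

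- Unadjusted n per group = 2(1.960 + 1.282)² / 0.43² = 113.6, so 114, against the stated 48.
- With adjustment, n = 113.6 × (1 − ρ²). Setting n = 48 gives ρ = √(1 − 48/113.6) = 0.76.
- With 48 per group, power is 0.56 unadjusted, 0.60 at ρ = 0.3, 0.68 at ρ = 0.5 and 0.84 at ρ = 0.7.

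The EPDS values in step 3 are all below 0.3, so adjusting for baseline EPDS alone leaves power at no more than about 0.60 on this reading.

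**The case against.** The strongest reply is that the article does not say what a critic might read into it.

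- **Separate, unadjusted tests.** A reader might infer these from the contrasts at four times. The text does not support that: no model is named, the power analysis refers to linear regression, and the contrasts could come from a repeated-measures model that includes baseline. A condensed article may also leave covariates to a fuller document. This stands. The supportable statement is that baseline appears in the list of contrasts and has no stated role as a covariate.
- **A descriptive baseline comparison.** The word contrasts might mean only that. It is possible, but with all tests at 0.05 and baseline listed beside the outcome visits, the wording invites testing. Nothing says that a baseline p-value would alter a later analysis, so no effect on the conclusions is shown.
- **A check on the randomisation process.** A baseline test could be defended this way, but the article does not give that purpose. The recorded, reproducible allocation scheme is better evidence.
- **The primary outcome.** The precision argument is weak here. Step 3 confirms this. If depression status is analysed as a category, the linear variance formula does not carry over directly.
- **Centre.** A reader might go on to claim that unstratified allocation over five centres distorts the result. Recruitment per centre is not given, nothing shows that centre predicts outcome, and chance imbalance does not bias a randomised comparison. Stratifying by centre is an optional design choice and no part of this point.

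**Conclusion.** The point holds in a limited form. A baseline significance test in this design examines only chance, with about a 23% probability of at least one spurious finding over five scores if they are independent. The baseline outcome values, collected before allocation, should be given a stated role as covariates.

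The benefit is uneven. It may be material for DASS-21 and C-PSOC (9 to 49% less variance at assumed correlations of 0.3 to 0.7). It is small for EPDS from its own baseline (about 1 to 8%, under the assumed slopes and SDs). Baseline DASS-21 depression has no entry window of its own and may add something for EPDS, but the article gives no basis for saying how much.

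Two stronger conclusions are not supported: that the plan commits to unadjusted analysis, and that adjustment would restore the stated 90% power. The second would need a correlation of about 0.76 on the standardised-difference reading, which the EPDS entry window makes implausible for baseline EPDS alone. The sample-size shortfall is a separate issue.

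**What to change.** Reword the Analysis section in four respects:

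1. Remove baseline from the list of contrasts. Present baseline characteristics and scores by arm descriptively, without significance tests.
2. State that the between-group contrasts at t1, t2 and t3 are each estimated from a model that includes the baseline value of the same outcome. A repeated-measures model that constrains the two arms to a common baseline mean would also serve.
3. For EPDS, add baseline DASS-21 depression as a covariate.
4. Say whether depression status is analysed as the score or as a category. If a category, use the corresponding adjusted binary model with the baseline EPDS score as covariate, since the baseline category is the same for all participants.

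Fix the covariates before anyone sees outcome data by arm, so that they cannot be chosen from observed imbalance.

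The cost is a few sentences. No new data are needed. Allocation follows completion of the baseline survey, so these covariates should be available for every randomised woman.
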